### Sample size calculation

Power/sample size calculations were made on the basis of an unadjusted Cox proportional hazards regression model. Within the primary analysis of aim 1, assuming a loss to follow-up of 20%, 570,000 subjects (285,000 with AF and 285,000 without) would have 90% power to detect a hazard ratio of 2, at an alpha of 0.05. This conservatively assumes an event rate of 22/100,000 per year in the exposed group (a rate of 45/100,000 is reported previously) [10] and an event rate of 11/100,000 per year in the unexposed group (a rate comparable to that reported previously) [15]. A query of the Medicare 5% sample between 2000 and 2015 reveals 818,940 unique patients with AF and 11,400 unique patients with a new diagnosis of CRAO. Power calculations were performed with the *powerSurvEpi* package (R v4.0.3).

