### Inclusion and exclusion criteria (Aim 2)

Inclusion criteria are fee-for-service Medicare enrollment for at least 12 consecutive month and 12 months FFS with Part A, B, and D enrollment following the index date for at least 12 months or until death, and presence of atrial fibrillation as defined in the exposure section. The index date for patients exposed to anticoagulation will be the date of the first anticoagulant prescription drug claim occurring after the diagnosis of AF. For potential controls, only patients with no exposure to anticoagulation throughout the study period would be eligible to avoid selecting controls who start an anticoagulant during the follow-up period. For controls, inclusion and exclusion criteria will be examined for each year after AF diagnosis, and the midpoint of one random year will be selected as the index date for each control patient.

Exclusion criteria include:

Patients with any claim for CRAO in the 12 months prior to AF diagnosis or index date for controls;Patients who die within first 12 months of enrollment;Patients taking therapeutic-dose heparin, enoxaparin, dalteparin, fondaparinux, or betrixaban.

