### Exposure

The primary exposure of interest is prevalent atrial fibrillation/atrial flutter. Atrial fibrillation/atrial flutter will be defined through ICD-9-CM 427.13 or ICD-10-CM code I48 in 2 outpatient claims or one inpatient claim within 365 days [16–18]. Episodes of atrial fibrillation within 1 month of inpatient surgery will be excluded to avoid including patients with isolated post-operative atrial fibrillation [19].

The secondary exposure of interest (among patients with atrial fibrillation) is exposure to anticoagulation. For our secondary analysis (Objective 2), we will utilize Medicare Part D prescription drug claims to identify patients taking a direct acting oral anticoagulant (DOAC) or warfarin.

A list of search terms to identify anticoagulant drugs will be utilized as per Table 1, below:

**Table 1 pone.0296251.t001:** Drug lookup queries for anticoagulant exposure.

Drug Name	
Warfarin	Part D claim for generic drug name like ‘%WARFARIN%’, summarized per month (90-day fills will be imputed to monthly indicators)
Apixaban	Part D claim for generic drug name like ‘%APIXABAN%’, summarized per month (90-day fills will be imputed to monthly indicators)
Dabigatran	Part D claim for generic drug name like ‘%DABIGATRAN%’, summarized per month (90-day fills will be imputed to monthly indicators)
Edoxaban	Part D claim for generic drug name like ‘%EDOXABAN%’, summarized per month (90-day fills will be imputed to monthly indicators)
Rivaroxaban	Part D claim for generic drug name like ‘%RIVAROXABAN%’, summarized per month (90-day fills will be imputed to monthly indicators)

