### Outcome

The outcome of interest is incident central retinal artery occlusion. Central retinal artery occlusion will be identified through ICD-9-CM 362.31, which we validated in a prior study [13] in the primary diagnosis position in any emergency department, inpatient, or outpatient claim. We will use the corresponding ICD-10-CM code H34.1x for claims occurring after September 31, 2015.

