#### Regression modeling (aim 2)

a) In keeping with target trial emulation methodology as described above, the index date for patients exposed to anticoagulation will be the date of the first anticoagulant prescription drug claim occurring after the diagnosis of AF. For potential controls, only patients with no exposure to anticoagulation throughout the study period would be eligible to avoid selecting controls who start an anticoagulant during the follow-up period. For controls, inclusion and exclusion criteria will be examined for each year after AF diagnosis, and the midpoint of one random year will be selected as the index date for each control patient.b) Similar to Aim 1, patients diagnosed with CRAO precedent to or concurrent to AF diagnosis will be excluded and these patients will be examined in an exploratory analysis.c) Our primary analysis will utilize propensity score overlap weighting methodology to approximate a randomized design where baseline hazard of CRAO of patients receiving anticoagulation vs. not receiving is comparable. We will incorporate the following variables to define the propensity score: age, time since first AF claim, sex, geography, race, Medicaid dual eligibility, vascular comorbidities and non-vascular comorbidities relevant to the likelihood that a patient will be treated with anticoagulation (to include all of the comorbidity variables included for Aim 1 propensity score, as well as history of gastrointestinal bleeding or peptic ulcer disease (using validated ICD-9-CM codes 531.x (gastric ulcer), 532.x (duodenal ulcer), and 578.x (gastrointestinal hemorrhage) and their ICD-10-CM counterparts K25.x, K26.x, and K92.2) and history of intracranial hemorrhage (any of ICD-10-CM I60, I61, S06.3, S06.4, S06.5, S06.6 and their ICD-9-CM counterparts 430.x, 431.x, 432.x)) [32–35].d) Our principal effect of interest is the hazard of CRAO among patients treated with any oral anticoagulant agent compared to those not treated. Given variable patient adherence to anticoagulation, we will take advantage of the strength of Part D data (which records pharmaceutical fills rather than prescriptions) and treat anticoagulation exposure as a time-varying covariate for patients exposed to anticoagulation.e) We will perform identical sensitivity analyses as described in Aim 1.f) Table shells for the results of Aim 2 are shown in Table 8.

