### Limitations

The principal limitation of this study is its observational, retrospective nature. Unfortunately, the incidence of CRAO is low, and evaluating the effect of anticoagulation on primary or recurrent CRAO risk is likely to be infeasible given the massive study sizes that would be required to detect an effect. While our target trial emulation methodology, including careful selection of index date and control patients and our use of overlap weighting methodology, can help to answer this question to its best extent using real-world data, the potential for residual confounding is still present in any observational data source. Additional limitations include the use of Medicare data, which has several intrinsic limitations, including having a limited number of beneficiaries under the age of 65, lacking access to clinical data not captured in structured claims, and limited ascertainment of key information on demographic identity, including gender identity and race/ethnicity. Another limitation in any non-controlled study of anticoagulation is the fact that the antithrombotic effect of anticoagulation varies according to patient adherence, especially for patients taking Warfarin. The use of Medicare Part D data has one major advantage in that it captures medication fills, not medication prescriptions, therefore giving a better surrogate of patient adherence, although some patients may not take medications that they nonetheless fill, recognizing that generalizability may be limited to Part D enrollees. Treating exposure to anticoagulation as a time-varying covariate will also help to capture more precisely the effect that therapeutic anticoagulation has on CRAO risk. Furthermore, our use of both positive and negative control endpoints in this analysis should help to interpret our eventual findings: existing evidence from randomized controlled trials has shown that use of anticoagulation is highly effective in preventing embolic stroke due to atrial fibrillation, and is associated with an increased risk of intracranial hemorrhage; if we replicate these results in our study design, it gives increased confidence that our results concerning CRAO may be valid. Finally, some patients with contraindication to oral anticoagulation may receive alternative management strategies that can decrease their ischemic stroke risk, such as receipt of a left atrial appendage occlusion device. We address this limitation through a sensitivity analysis excluding any patient who receives a LAAO during the study follow-up period or with a diagnostic code indicating the placement of an LAAO in the comorbidity ascertainment window.

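### Aim 2 reads anticoagulant exposure from Part D fills alone, so treated patients whose facility stay outlasts their filled supply are probably coded unexposed; this bears mainly on the control endpoints

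*Protocol article*

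**What the plan says.** The Exposure section of the protocol article names one source for Aim 2: "we will utilize Medicare Part D prescription drug claims to identify patients taking a direct acting oral anticoagulant (DOAC) or warfarin". Table 1 lists warfarin and four DOACs, each "summarized per month (90-day fills will be imputed to monthly indicators". Regression modeling (aim 2), item d, will "treat anticoagulation exposure as a time-varying covariate for patients exposed to anticoagulation". Under Inclusion and exclusion criteria (Aim 2), on the control side, "only patients with no exposure to anticoagulation throughout the study period would be eligible". Aim 2 also requires Part A enrolment.

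Outcomes are counted in acute care as well as outside it. CRAO counts "in the primary diagnosis position in any emergency department, inpatient, or outpatient claim". Regression modeling (aim 1), items f and g, defines ischemic stroke from hospitalizations and ED visits in the primary position, and urinary tract infection from hospital or ED care with no diagnosis position given. Table 8 carries both into Aim 2 and adds intracranial hemorrhage.

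Limitations presents Part D as a strength because it "captures medication fills, not medication prescriptions, therefore giving a better surrogate of patient adherence", and adds: "Treating exposure to anticoagulation as a time-varying covariate will also help to capture more precisely the effect". Its one caveat about the fills as a measure of exposure is that a filled drug may not be taken. The reverse case, drug taken without a fill, is not considered.

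**The concern.** With a time-varying indicator, a treated patient's months without fill coverage count as unexposed. Such a month normally suggests that treatment has lapsed. During a long facility stay it may only mean that the facility supplied the drug. The patient is then treated and enrolled in Part D, but the exposure source cannot see the treatment.

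The error is one-sided. It affects only ever-treated patients, and it moves their time and events into the unexposed category. If event rates in those months exceed community rates, the unexposed rate is inflated and anticoagulation looks more protective than it is.

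This matters most for the plan's own validity check. Limitations says that reproducing the known effects of anticoagulation on embolic stroke and intracranial hemorrhage would raise confidence in the CRAO result, and urinary infection is the negative control. The misclassification could help produce the expected stroke result, hide part of an expected hemorrhage increase, and make urinary infection look prevented.

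**Working it through.** The article gives no Aim 2 figure to reproduce. Its only sample size is for Aim 1 and does not bear on this point.

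**What the text fixes.** Source: Part D fills. Unit: month. 90-day fills are spread over months. The indicator is time-varying. Events in inpatient claims count. No rule is given for facility months.

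**Assumptions (none is in the article).**
- Drug supplied within a Part A stay creates no Part D claim.
- f = share of time spent in facilities: 2% or 4%, the same in on-drug and unexposed time.
- m = facility event rate relative to the community rate: 3 or 5, with 1 as the null case.
- R = unexposed person-time per unit of on-drug time: 0.5 or 1.
- g = share of treated patients' facility time still covered by an earlier fill: 0, 0.5 or 0.8.

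**Model.** Set on-drug time to 1 and the unexposed community rate to 1; h is the true hazard ratio.
- Coded exposed: time = (1 − f) + fg; events = h[(1 − f) + fgm].
- Coded unexposed: time = R + f(1 − g); events = R[(1 − f) + fm] + f(1 − g)mh.
- Observed ratio = exposed rate / unexposed rate.

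**Largest shift at half coverage** (h = 0.70, f = 0.04, m = 5, R = 0.5, g = 0.5):
- Exposed rate: 0.70 × (0.96 + 0.10) / 0.98 = 0.742 / 0.98 = 0.757.
- Unexposed rate: [0.5 × (0.96 + 0.20) + 0.02 × 5 × 0.70] / 0.52 = 0.65 / 0.52 = 1.25.
- Observed: 0.757 / 1.25 = 0.61.

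**Smallest shift at half coverage** (f = 0.02, m = 3, R = 1, g = 0.5):
- Exposed rate: 0.707 / 0.99 = 0.714.
- Unexposed rate: (1.04 + 0.021) / 1.01 = 1.050.
- Observed: 0.714 / 1.050 = 0.68.

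**Range over all f, m (3 or 5) and R:**

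| True HR | No coverage (g = 0) | Half covered | 80% covered |
|---|---|---|---|
| 1.00 | 0.69–0.93 | 0.83–0.96 | 0.93–0.99 |
| 0.70 | 0.53–0.66 | 0.61–0.68 | 0.66–0.69 |
| 0.50 | 0.40–0.48 | 0.45–0.49 | 0.48–0.50 |

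**Sensitivity to the assumptions.**
- With m = 1 and no coverage, 0.70 appears as 0.70–0.72.
- With m = 1.5 and half coverage, 0.70 appears as 0.69–0.70.
- With full coverage (g = 1) there is no shift.
- If unexposed time carried no facility excess (replace R[(1 − f) + fm] by R), 0.70 would appear as 0.59–0.69 with no coverage and 0.69–0.72 with half coverage. The equal-share assumption therefore also drives the result.

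**The case against.** **The premise lies outside the document.** The article does not say that facility-supplied drug is absent from Part D, and it gives no facility share of time and no facility event rate. This stands. The premise is general knowledge of the data source and is labelled as an assumption, and the size can only be shown as a range.

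**A full analysis plan may hold the rule.** It may. But the article does not leave exposure construction open: it fixes the source, drug list, unit and 90-day-fill handling, and it claims a precision advantage for the result. As stated, the rule is incomplete in one direction.

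**A reader might infer that every treated patient in a facility is counted as unexposed, just when risk is highest.** The document does not support this. Monthly indicators and spread 90-day fills keep a short stay, or any stay under a current fill, coded as exposed. Nor does the article say that event risk is higher in facilities.

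**Outcome coding limits the mechanism.** CRAO and ischemic stroke count only in the primary diagnosis position, which mainly captures the reason for an encounter. Complications arising during an admission for something else would mostly not count, and a stay that follows a first stroke is no longer time at risk for that endpoint. This largely stands for stroke during hospital time. It does not remove long skilled-nursing stays, from which a patient can be sent to hospital or an ED with a new event. It also gives less protection to urinary infection, for which no diagnosis position is stated.

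**Conclusion.** The point holds in limited form. On the stated text, a treated patient whose stay outlasts the filled supply is coded unexposed, provided that facility-supplied drug leaves no Part D claim. The affected time is mainly long, chiefly skilled-nursing, stays.

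The direction is toward apparent protection if event rates in those months are raised and unexposed time has a similar facility share. The half-coverage range of 0.61 to 0.68 for a true 0.70 is a fairer illustration than the no-coverage range of 0.53 to 0.66, because the latter lets no facility month be covered by an earlier fill. Neither is an estimate for this study.

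A reader might conclude that the CRAO hazard ratio is materially biased. The article does not support that: nothing in it suggests that CRAO risk rises in facilities, and without a rate difference the shift is trivial. What is weakened is the use of the urinary infection, intracranial hemorrhage and stroke endpoints as evidence of validity.

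**What to change.** In the Aim 2 exposure rule, use Part A inpatient and skilled-nursing dates when building the monthly indicator: carry the exposure status at admission through the stay and shift unused supply forward to discharge. Add a sensitivity analysis that removes facility months, both events and person-time, from treated and control patients alike. Add a sentence to Limitations saying that Part D fills may not show drug supplied during facility stays.

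The cost is a few lines of text and some programming. Part A enrolment is already an Aim 2 requirement, so the stay dates should be available. The downside is that carrying status forward assumes treatment continues during the stay, which can misclassify in the other direction. The sensitivity analysis tests that assumption.

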### Prior work addressing this question

There is a higher burden of AF in people with CRAO than in the general population. One prior insurance-based cohort study in Taiwan described a higher incidence of CRAO in patients with AF than in the general population [10]. This study adjusted for age, sex and year of presentation but did not adjust for vascular risk factors or medication exposures. Additionally, other studies have reported a higher prevalence of AF in patients with CRAO [11, 12] than in the general population which lends credence to the hypothesis that the two conditions are associated. However, CRAO (like cerebral stroke) is a surrogate marker for vascular risk [8] so studies that comprehensively address this confounding are needed. We performed a study using healthcare cost and utilization project (HCUP) data from New York, California, and Florida hospitalizations and emergency department visits found that there was an inverse relationship between AF and CRAO [13]. However, this study lacked access to outpatient and prescription drug information, which resulted in systematic under-ascertainment of both AF and CRAO. Furthermore, this study could not evaluate whether exposure to anticoagulation in patients with AF could prevent the development of CRAO. Therefore, a study using inpatient, outpatient, and pharmacy claims data would be essential to definitively determine whether cardioembolism is a potential causative etiology for CRAO, and whether anticoagulation can modify this risk factor. That only 50–60% of people meeting guideline criteria for anticoagulation for AF are actually treated with an anticoagulant creates an intriguing opportunity to leverage real-world data to conduct a quasi-randomized study to examine the interplay between anticoagulation and CRAO risk [14].

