#### Descriptive analysis

Using the weighted analytic cohort, we will calculate means with standard deviations and medians with interquartile ranges to summarize the distribution of continuous, normally distributed variables, and medians with interquartile ranges to summarize the distribution of continuous, not normally distributed variables. We will summarize categorical data using counts with percentages. Data will be stratified by presence of atrial fibrillation and include key demographic and clinical factors. For Aim 2, we will additionally summarize anticoagulant usage patterns among patients with atrial fibrillation, including class of agent utilized (DOAC vs. warfarin), number of monthly fills per calendar year, and duration of exposure in months. Table shells are provided in Tables 3–5.

**Table 3 pone.0296251.t003:** Characteristics of the overlap-weighted primary analysis cohort defined at first date of meeting study eligibility.

Characteristic	Total Sample (N = xxxx)	Patients with AF (n = xxxx)	Patients without AF (n = xxxx)	Standardized Difference
Age, mean (SD)				
Women, n (%)				
Race/ethnicity, n(%)				
Asian/Pacific Islander				
Black, non-Hispanic				
Hispanic				
White, non-Hispanic				
Comorbidities (n, %)				
Cerebrovascular Disease				
Chronic Kidney Disease				
Congestive Heart Failure				
Coronary Artery Disease				
Diabetes Mellitus				
Hyperlipidemia				
Hypertension				
Peripheral Vascular Disease				
Smoking				

**Table 4 pone.0296251.t004:** Characteristics of the secondary analysis (Part-D enrolled) cohort defined at first date of meeting study eligibility.

Characteristic	Total Sample (N = xxxx)	Patients with at least one fill for anticoagulant (n = xxxx)	Patients without any anticoagulant use (n = xxxx)	Standardized Difference
Age, mean (SD)				
Women, n (%)				
Race/ethnicity, n(%)				
Asian/Pacific Islander				
Black, non-Hispanic				
Hispanic				
White, non-Hispanic				
Comorbidities (n, %)				
Cerebrovascular Disease				
Chronic Kidney Disease				
Congestive Heart Failure				
Coronary Artery Disease				
Diabetes Mellitus				
Hyperlipidemia				
Hypertension				
Peripheral Vascular Disease				
Smoking				
Antiplatelet agent use				
Oral anticoagulant use				
Lipid-lowering agent				
Oral hypoglycemic agent				
Oral antihypertensive agent				

**Table 5 pone.0296251.t005:** Anticoagulation usage patterns among patients with atrial fibrillation with at least one Part D fill for an anticoagulant medication.

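### In Aim 2, never-anticoagulated control status rests only on the absence of a Part D claim, so users supplied wholly outside Part D can enter the control arm and dilute the hazard ratios

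*Protocol article*

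**What the plan says.** The Exposure section states that for Aim 2 "we will utilize Medicare Part D prescription drug claims to identify patients taking a direct acting oral anticoagulant (DOAC) or warfarin". Table 1 puts this into operation for warfarin and four DOACs. Every row is a drug-name search in Part D, for example "Part D claim for generic drug name like ‘%WARFARIN%’, summarized per month".

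On controls, Regression modeling (aim 2), item a, says that "only patients with no exposure to anticoagulation throughout the study period would be eligible". The Aim 2 inclusion criteria repeat the rule. Neither place names a source other than Part D for confirming non-exposure. The Table 4 shell then contrasts patients with at least one fill against patients with no anticoagulant use of any kind.

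The Aim 2 inclusion criteria require "12 months FFS with Part A, B, and D enrollment following the index date for at least 12 months or until death". Within the exposed group, the plan will "treat anticoagulation exposure as a time-varying covariate for patients exposed to anticoagulation".

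The Limitations section discusses adherence, drugs that are filled but not taken, and generalizability to Part D enrollees. It does not mention anticoagulants taken without a Part D claim.

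**The concern.** The control definition is a statement about drug use, but the data behind it are about one payer's claims. Being enrolled in Part D means that a fill can be recorded there. It does not mean that every fill is. A person who pays cash or uses other coverage for every fill leaves no Part D record and is classed as never exposed.

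Treated people among the controls lower the control hazard where the drug protects and raise it where the drug harms. Both pull the hazard ratio toward 1. That affects the principal Aim 2 effect, for an outcome that the Limitations section itself describes as rare. It also affects the stroke and intracranial hemorrhage results, which the same section relies on to lend credibility to the CRAO result. A weak or null Aim 2 finding would then be harder to interpret.

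**Working it through.** **The plan's own figure.** There is none to reproduce. The only sample-size statement is for Aim 1, and this point does not touch it. Aim 2 states no effect size, event count or power.

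**Inputs**
- Treated share T of patients with atrial fibrillation: the introduction (Prior work addressing this question) says "only 50–60% of people meeting guideline criteria for anticoagulation for AF are actually treated with an anticoagulant". I use 50% to 60%, with 55% as the centre. Applying a share of guideline-eligible patients to the Aim 2 cohort is an assumption.
- Share q of all users who have no Part D fill at all: not in the documents; assumed 2% to 30%.
- True hazard ratio t: not in the documents; assumed 0.50 or 0.70 for benefit and 2.0 for a harm.

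**Step 1: dilution.** Let c be the share of controls who are really treated. Their hazard is t times that of the untreated, so the control arm's average hazard is (1 − c) + c·t times the untreated hazard. Hence

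observed HR = t / ((1 − c) + c·t).

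For t = 0.50 and c = 10%: 0.50 / (0.90 + 0.05) = 0.526.

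| c | true 0.50 reads | true 0.70 reads |
|---|---|---|
| 5% | 0.51 | 0.71 |
| 10% | 0.53 | 0.72 |
| 20% | 0.56 | 0.74 |
| 30% | 0.59 | 0.77 |

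A true 2.0 reads 2/1.10 = 1.82 at c = 10% and 2/1.20 = 1.67 at c = 20%.

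**Step 2: how much leakage would produce such a c.** Hidden users join the untreated in the control pool, so

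c = T·q / ((1 − T) + T·q).

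At T = 55%, q = 10% gives 0.055/0.505 = 10.9%, and q = 20% gives 0.11/0.56 = 19.6%. Solved for q, q = c(1 − T) / (T(1 − c)). So c = 20% needs 0.09/0.44 = 20% of all users without a single Part D fill, and c = 30% needs 0.135/0.385 = 35%. Over T = 50% to 60% and q = 2% to 30%, a true 0.50 reads between 0.505 and 0.592.

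**Step 3: cost in events.** The events needed scale with 1/(ln HR)², so the inflation is (ln t / ln observed HR)². At T = 55% and t = 0.50:

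| q | c | observed HR | events needed, relative |
|---|---|---|---|
| 5% | 5.8% | 0.515 | 1.09 |
| 10% | 10.9% | 0.529 | 1.18 |
| 20% | 19.6% | 0.554 | 1.38 |

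For illustration, 88 events give 90% power for a hazard ratio of 0.50 with equal arms and two-sided alpha 0.05 (Schoenfeld). With those 88 events, power falls to 84.8% at c = 10.9% and to 79.0% at c = 19.6%.

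**Step 4: what other claims are available.** The introduction argues that "a study using inpatient, outpatient, and pharmacy claims data would be essential", and Table 2 already uses diagnosis codes and, for tobacco, procedure codes. The material for a cross-check is therefore in the study. The article names no anticoagulant-use diagnosis code or INR-test code, and it gives no sensitivity for either.

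**The case against.** Several counter-arguments carry weight.

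- **The premise is not in the documents.** Nothing in the article says how often enrollees are supplied outside Part D. This stands: the size is an assumption throughout.
- **The control rule is strict.** One captured fill at any time in the study period removes a person from the controls, so only someone whose every fill escapes Part D contaminates the arm. This stands too, and step 2 shows that the upper half of the range needs substantial leakage that nothing in the documents supports.
- **Stroke and hemorrhage act as a check.** Gross misclassification should show as failure to reproduce their known effects. This is partly right. At 5% to 10% contamination the shift is too small for that check to notice, and a failure would not identify its cause.
- **Direction.** The formula assumes that hidden users share the baseline risk and benefit of other users. If they differ, confounding could add to the dilution or offset it. Pure dilution would not create a false protective effect.
- **An article condenses a fuller plan.** Extra code lists may sit elsewhere. But the exposure and control definitions are written out here in full, and the point concerns what they fix.

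A reader might also infer that diagnosis and INR claims would reveal all of these users. The documents do not support that. INR tests point mainly to warfarin users, not to users of the four DOACs in Table 1, and tests not billed to Medicare stay unseen.

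**Conclusion.** The point holds in a limited form. Control status is inferred from the absence of one type of claim, no second source is planned, and the Limitations section covers only the opposite error (filled but not taken). Under the stated assumptions the bias is toward 1. It is modest at 5% to 10% contamination (0.50 reads 0.51 to 0.53) and more noticeable at 20% (0.56).

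These figures rest on an assumed share, proportional hazards, and hidden users who resemble other users and are treated throughout. A reader might conclude that Aim 2 is seriously biased. The documents do not show that, because they give neither the share nor the true effect. The revision is worthwhile because it is cheap and would replace a pure assumption with a count, although confidence in the size of the problem is low.

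**What to change.** 1. At index, exclude patients who have a long-term anticoagulant-use diagnosis code or repeated INR-monitoring claims in the 12-month look-back without a matching Part D fill. If the primary definition is to stay as it is, prespecify this exclusion as a sensitivity analysis.
2. Report how many controls are flagged. Because the codes will miss some users, the count is a guide to the problem and not a full measure of it.
3. Describe the control arm in the text and in Table 4 as *no Part D anticoagulant fill*, and add the limitation.

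These codes should not be used to start exposed time during follow-up. A diagnosis code or an INR test gives no drug and no days' supply, so it cannot feed the monthly indicators in Table 1. It would also turn never-exposed controls into exposed patients, against the Aim 2 definition.

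The cost is two code lists, one eligibility or sensitivity rule and one count. The downside is that some truly untreated patients with stray codes are dropped. Also, Part D enrollment is spelled out only for the period after index, so a look-back code without a fill may reflect time before Part D enrollment; such patients should be counted separately.
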